### Interventions

Patients in both treatment groups have the affected shoulder immobilized in a fixed sling for 2 weeks followed by 3 weeks in a non-fixed sling. The PR group starts loading (assisted active range of motion (AAROM) and active range of motion (AROM)) from week 2, while this is introduced in the UC group from week 6. The PR group is attending individual physiotherapist-supervised exercise therapy three times weekly, supplemented with daily home exercises (week 2, 3, 4 and 5), and the UC group is attending individual physiotherapist-supervised exercise therapy once a week supplemented with daily home exercises (week 2, 3, 4 and 5). From weeks 6 to 12 all patients receive physiotherapist-supervised exercise therapy twice a week (individually or in small groups) next to the self-administered exercise once a week (Table 1). Descriptions of on-site and home interventions are found in the additional files (Additional files 1 and 2).

**Table 1 Tab1:** Overview of the postoperative intervention in main trial

Week	Progressive rehabilitation (PR)	Week	Usual care (UC)
1- 5	Shoulder immobilized in standard sling.	1- 5	Shoulder immobilized in standard sling.
2- 5	Physiotherapist guided PROM exercises PROM Restrictions: ABD + FLEX: None IR < 90 degrees in neutral ER < 45 degrees in neutral	2- 5	Physiotherapist guided PROM exercises PROM Restrictions: ABD + FLEX: None IR < 90 degrees in neutral ER < 45 degrees in neutral
2	Close-chain AAROM and AROM exercises AAROM and AROM Restrictions: ABD + FLEX < 90 degrees IR < 90 degrees in neutral ER = 0 degrees in neutral		
3- 5	Close-chain AAROM and AROM exercises AAROM and AROM Restrictions: ABD + FLEX < 90 degrees IR < 90 degrees in neutral ER < 45 degrees in neutral		
6-12	Therapist-supervised AROM (FLEX, ABD, EXT, ER and IR) with gradually (individually) increased loading and progression from close-chain to open-chain exercises.	6-12	Therapist-supervised AROM (FLEX, ABD, EXT, ER and IR) with gradually (individually) increased loading and progression from close-chain to open-chain exercises.
12-20	Continuation of rehabilitation in the community	12-20	Continuation of rehabilitation in the community

*PR* progressive rehabilitation, *UC* usual care, *ROM* range of motion, *PROM* passive range of motion, *ABD* abduction, *FLEX* flexion, *IR* Internal rotation, *ER* external rotation, *AAROM* assisted active range of motion, *AROM* active range of motion, *EXT* extension

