### Treatment adherence

Intervention adherence and attendance (on site and home-based) within the 12 weeks is recorded in exercise logbooks for both groups. In the exercise logbook, the patients are asked to report completed home-based exercise sessions and reasons for non-completed sessions (pain or other reasons). Supervision of the subsequent home exercises at the commencement of every session is performed to facilitate program adherence. Reinforcement techniques are used with the physiotherapist giving positive feedback and commending patients for their efforts.

As part of the post-operative standard medical treatment package all patients are offered paracetamol and non-steroidal anti-inflammatory drugs (NSAIDs) as basic pain treatment supplemented with morphine if necessary, and medication is prescribed before inclusion and randomization. Concomitant private physiotherapy sessions, acupuncture or other healthcare initiatives are prohibited during the trial. The available exercise equipment during the supervised rehabilitation includes Steens Physical Double Handle Speed Pulley (weight interval 0.5–2 kg) (Proterapi), Thera-Band System of progressive exercise, carpet tile, jump rope and broomstick. Also, sloping board (for supine elevation exercise in the scapular plane), ProFitter and various vinyl-coated hand weights produced by Trendy Sport will be available.

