### Statistical analysis plan

The primary efficacy analysis performed is assessment of the between-group difference in change in the WORC score after 12 weeks in the ITT population. The ITT population is defined as all randomized patients irrespective of compliance or withdrawals. Missing data will be replaced using a multiple imputation technique with age, gender, center, group allocation (masked) and baseline values as predictors. For sensitivity purposes missing data will be imputed using baseline observation carried forward (BOCF). The modified ITT population is defined as the ITT population that has a valid baseline observation of the variable of interest. The as-observed (AO) population is defined as patients who have the outcome of interest assessed at a given time point of interest (i.e. no imputation of missing data will be done).

The per-protocol (PP) population is defined as patients in the AO population that adhere to this protocol, defined by the criteria of the two groups: the PR group (Table 1), included in the AO population and have attended at least 75% of the scheduled rehabilitation appointments, whether at clinical visits or home-based as tailored to the individual (documented by the exercise logbook), and do not stop the intervention during the 12-week main trial period and do not engage in concomitant exercise therapy (e.g. private physiotherapy sessions, acupuncture); and the UC group (Table 1), included in the AO population, and do not stop the intervention during the 12-week main trial period and do not engage in concomitant exercise therapy. Each patient registers the home shoulder exercises in an exercise logbook, and successful completion of the intervention is defined as performance of 75% of the planned exercises.

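### The per-protocol set carries a 75% attendance threshold in the PR arm only, and a later sentence leaves unclear whether UC patients face one too

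*Protocol article*

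**What the plan says.** All of the following is in the protocol article.

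- Statistical analysis plan, PR criterion: the patient belongs to the as-observed (AO) population, does not stop the intervention, has no concomitant exercise therapy, and must "have attended at least 75% of the scheduled rehabilitation appointments, whether at clinical visits or home-based as tailored to the individual".
- Statistical analysis plan, UC criterion: "the UC group (Table 1), included in the AO population, and do not stop the intervention during the 12-week main trial period", again with no concomitant exercise therapy. No attendance threshold appears.
- Statistical analysis plan, end of the same paragraph: after noting that each patient keeps a logbook of home exercises, it states that "successful completion of the intervention is defined as performance of 75% of the planned exercises". It does not say whether this governs PP membership.
- Interventions: usual care has a schedule to adhere to. In weeks 2 to 5 "the UC group is attending individual physiotherapist-supervised exercise therapy once a week supplemented with daily home exercises", and in weeks 6 to 12 both arms have two supervised sessions a week.
- Treatment adherence: "Intervention adherence and attendance (on site and home-based) within the 12 weeks is recorded in exercise logbooks for both groups".
- Statistical analysis plan, primary analysis: "The primary efficacy analysis performed is assessment of the between-group difference in change in the WORC score after 12 weeks in the ITT population".

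**The concern.** A per-protocol comparison is interpretable only if the arms are filtered in the same way. Here one arm is filtered on attendance and the other, on the text as it stands, is not. In weeks 6 to 12 supervised frequency is the same in both arms. A PR patient who misses enough of those sessions leaves the PP set, while a UC patient who misses the same ones stays.

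Attendance is plausibly related to outcome. The Treatment adherence section has patients record why home sessions were missed and names pain as one reason. Removing low attenders from a single arm can then shift that arm's mean with no treatment effect at all.

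The closing 75% sentence adds a second problem. If it is a PP condition, UC patients do face a threshold, but on a different denominator (planned exercises rather than scheduled appointments), and PR patients face two. If it is not, the asymmetry stands. Two analysts could build different PP sets from this paragraph.

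**Working it through.** **Criteria side by side**

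| Condition | PR | UC |
|---|---|---|
| In AO population | yes | yes |
| Did not stop the intervention | yes | yes |
| No concomitant exercise therapy | yes | yes |
| At least 75% of scheduled appointments | yes | not stated |
| 75% of planned exercises (completion sentence) | unclear | unclear |

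**Could the rule be applied to UC?** Supervised sessions from the Interventions section, counting four weeks (2–5) and seven weeks (6–12):

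- PR: 3×4 + 2×7 = 26; 75% is 19.5, so 20 sessions.
- UC: 1×4 + 2×7 = 18; 75% is 13.5, so 14 sessions.

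Home sessions come on top in both arms. UC therefore has a countable schedule, and the logbooks supply the data.

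**Size of the possible distortion.** The plan gives no figure to reproduce here. The Sample size section supplies SD 20 and a target difference of 12 points. The fraction q of PR patients below the threshold and the correlation r between attendance and WORC change are assumptions. Removing the lowest fraction q on a normally distributed attendance variable, in PR only and with no treatment effect, shifts the PR mean by

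shift = r × 20 × φ(z_q) / (1 − q),

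where z_q is the standard normal q-quantile and φ the normal density.

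| q | φ(z_q)/(1−q) | r = 0.2 | r = 0.3 | r = 0.4 |
|---|---|---|---|---|
| 0.15 | 0.274 | 1.1 | 1.6 | 2.2 |
| 0.25 | 0.424 | 1.7 | 2.5 | 3.4 |
| 0.35 | 0.570 | 2.3 | 3.4 | 4.6 |

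The range is 1.1 to 4.6 points, or 9% (1.1/12) to 38% (4.6/12) of the target difference.

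**Sign.** The formula is linear in r, so a negative correlation gives a negative shift. At r = −0.2 with 20% removed it is −1.4 points, against PR.

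**False-positive rate of the PP test.** This takes 41 UC patients, 41×(1−q) PR patients, a two-sided 5% test, and the PR variance reduced for truncation. For r = 0.3 and q = 0.30 the shift is 2.98 and the standard error is √(19.5²/28.7 + 20²/41) ≈ 4.8. The ratio of 0.62 gives a rejection rate of 0.095. Other cases:

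- r = 0.1, q = 0.20: shift 0.7, rate 0.053
- r = 0.2, q = 0.20: shift 1.4, rate 0.060
- r = 0.4, q = 0.40: shift 5.2, rate 0.18

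**Under a common threshold** the shift is zero with no treatment effect, provided attendance and its relation to outcome are the same in both arms.

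**The case against.** Four points can be made for the plan.

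1. The completion sentence refers to each patient and sits in the PP paragraph, so UC may have been meant to meet a 75% standard. That is possible, but the sentence is not worded as a membership condition and uses a different denominator. It makes the definition ambiguous and does not cure the asymmetry.

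2. A reader might infer that the PP analysis is biased by construction towards PR. The documents do not support that. They report no relation between attendance and outcome, and pain is only one of the reasons for missed sessions that the logbook allows. If patients who recover well skip sessions, the distortion goes the other way. A shift towards PR is the likelier direction, but it is not shown. This objection stands.

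3. The illustration may run high. Both arms already exclude patients who stop, lack the outcome or seek other therapy, so some of those with the worst course leave both arms before the threshold acts. The central 2.5 points is also only about half a standard error: with 31 PR and 41 UC patients, 20×√(1/31 + 1/41) ≈ 4.8. This stands as a caution on size. For the same reason UC patients are unselected only for attendance, not altogether.

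4. A reader might infer that the trial's superiority claim is at risk. It is not: the primary analysis is ITT, the plan assigns no efficacy conclusion to PP, and the Background and Discussion fault earlier trials for per-protocol analyses. This stands and limits the weight of the point.

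**Conclusion.** The PP definition is asymmetric as written, and the completion sentence makes it ambiguous as well. Both facts come directly from the text. Lack of data does not explain the difference, because attendance is logged in both arms.

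The consequence is confined to a non-primary analysis. With 15–35% of PR patients below the threshold, a correlation of 0.2–0.4 and SD 20, the PP contrast would move by about 1 to 5 points towards PR with no treatment effect. Those inputs other than the SD are assumptions, and a negative correlation reverses the sign. What is established is that the two PP groups are selected differently; the direction and size of the resulting bias are not. The definition should be corrected before the PP set is built.

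**What to change.** Replace the two arm-specific criteria with one rule for both: in the AO population, at least 75% of the sessions scheduled for the patient's own arm as documented in the logbook, no stop of the intervention during the 12-week period, and no concomitant exercise therapy. State whether clinic and home sessions are pooled in the denominator. Then either make the completion sentence the same rule or say that it is descriptive and does not determine PP membership. Report PP as supportive of the ITT result.

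The change takes a sentence or two and no new data collection. The UC part of the PP set becomes somewhat smaller. A common threshold removes the built-in asymmetry but not all selection bias. The schedules differ (about 26 against 18 supervised sessions), and if attendance, or its relation to outcome, behaves differently by arm, the PP groups can still differ. The report should say so.

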### Sample size and power considerations

The sample size is calculated to test the superiority of the PR protocol over the UC protocol in the assessment of change in the WORC physical symptoms subscale at week 12 (primary outcome) [75]. With 41 patients per group, the study will have 80% power assuming the expected group difference in the mean changes from baseline is 12 points, corresponding to the suggested minimum clinical relevant difference [47], the common standard deviation is 20 (0–100 scale) [75] and a significance level of 5%. With an expected dropout around 20% during the study we will randomize and allocate 100 patients (50 to each group); analyzing the intention to treat (ITT) population, which will give power of 85% to detect the aforementioned difference. A provisional deadline for patient recruitment is set to June 2018, but in case the target number of 100 patients has not been met the recruitment period may be extended to reach the number required (2 times 41 patients) to obtain power of at least 0.8 (80%).

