The primary analysis at week 12 will be by analysis of covariance (ANCOVA) on change from baseline in the WORC domains as dependent variables, with group allocation (two levels) and time (week 6 and 12), gender and site as fixed factors, whereas age and baseline values will be analyzed as covariates. Secondary outcome measures will be analyzed by multiple logistic regression for binary outcome measures (re-tear, tendon healing, recurrence of symptoms (e.g. pain and function), complications) and by ANCOVA for the continuous outcome measures (pain, patient-reported outcomes, surgery information, strength, ROM) as dependent variables (individually), with group allocation and time as fixed factors, and site and baseline values as covariates. Predictors of health outcomes will be analyzed by ANCOVA or multiple regression as independent variables, with change in the WORC as the dependant variable. All statistical tests will be two-sided and statistical significance will be denoted by a computed *p* value equal to or less than 0.05. All data analysis will be carried out according to a pre-established analysis plan. The statistical analysis plan (SAP) will be carried through blinded according to group allocation, and results will be interpreted in an author consensus statement prior to disclosing/revealing group allocation on the basis of a blinded review of the data from the primary endpoint (changes from treatment A compared to changes from treatment B), assuming that treatment A is the active treatment (PR), and the other assuming that treatment B is the active treatment (UC). Analysis of the primary outcome will be calculated blinded, and two interpretations will be performed based on whether PR or UC is superior. Not until signed consent from all of the authors of this trial (identical to the authors of this SAP) has been obtained, agreeing on one interpretation of the results only, will the randomization code be broken. This is to reduce bias in the interpretation of the current findings. On agreement, all members of the author group will approve and sign the interpretations before any publication procedures are initiated [76].

The protocol conforms to the recommendations of the Enhancing the Quality and Transparency Of health Research (EQUATOR) network [77] using the Standard Protocol Items: Recommendations for Interventional Trials (SPIRIT) checklist and the Consolidating Standards of Reporting Trials (CONSORT) statement [78] (Additional file 3).

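### As written, the primary ANCOVA estimates the average of the week-6 and week-12 group differences, not the week-12 difference declared as primary

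*Protocol article*

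**What the plan says.** The target is stated several times and always as week 12. The opening of Methods/design puts the primary endpoint 12 weeks from baseline. Outcome measures/variables defines the primary outcome as the 12-week change in WORC. The Statistical analysis plan section describes the primary efficacy analysis as assessing the "between-group difference in change in the WORC score after 12 weeks in the ITT population".

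The sample size section sizes the trial on one comparison of two means at that visit: "the expected group difference in the mean changes from baseline is 12 points", SD 20, and "a significance level of 5" per cent.

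Later in the Statistical analysis plan section, the model for this analysis is an ANCOVA on change from baseline "with group allocation (two levels) and time (week 6 and 12), gender and site as fixed factors". Age and the baseline value are covariates. The text mentions no interaction of group with time, no contrast at week 12, and no patient effect or covariance for repeated visits. Tests are two-sided at 0.05.

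Continuous secondary outcomes are to be analysed by ANCOVA "with group allocation and time as fixed factors, and site and baseline values as covariates". The visits that make up time are not listed for these models.

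**The concern.** The declared target and the declared model do not match. If the analyst follows the model sentence literally, the single group coefficient answers whether the arms differ on average over weeks 6 and 12, while the trial claims to answer whether they differ at week 12.

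The difference could matter in this trial. According to the Interventions section, the arms differ in weeks 2 to 5, both in when active loading starts and in the number of supervised sessions. From weeks 6 to 12 they follow the same supervised schedule. The week-6 assessment therefore falls where the regimens converge, and a group difference that grows or fades between the two visits is plausible. An early difference that has gone by week 12 could be reported as a positive primary result. A difference that appears only by week 12 could be diluted and missed.

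The second matter is precision. Two visits from one patient are correlated. If the ANCOVA treats them as independent rows, its standard errors are too small.

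**Working it through.** **The plan's own figures.** Inputs from the sample size section: difference 12, SD 20, two-sided 5%. For 80% power, n per group = 2 × (1.96 + 0.842)² × 20² / 12² = 43.6, so 44. The stated 41 per group gives 77.5% power (normal) or 76.5% (t), so that figure does not reproduce. The stated 85% with 50 per group does (85.1% normal, 84.4% t). The shortfall at 41 is a separate matter. What counts here is that the calculation is a single-visit comparison, consistent with a week-12 target.

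**Step 1: which rows are in the model.** If only week-12 data were used, time would be constant and could not be a factor. A time factor with levels week 6 and week 12 requires two rows per patient.

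**Step 2: what the group coefficient estimates.** Write d6 and d12 for the true group differences at the two visits. Each patient contributes one row per visit (missing values are to be imputed), so group and time are balanced against each other. The main-effects coefficient for group is then (d6 + d12) / 2, whatever the correlation between visits.

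The assumed effects below are illustrations, not figures from the protocol. The listed model was simulated with 50 per group, residual SD 20, residual correlation 0.5 and independent errors, 2,000 runs per row.

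| d6 | d12 | (d6 + d12)/2 | Listed model: estimate, rejection | Week-12 ANCOVA: estimate, rejection |
|---|---|---|---|---|
| 0 | 12 | 6 | 5.9, 52% | 12.0, 82% |
| 12 | 0 | 6 | 6.1, 54% | 0.2, 4.6% |
| 6 | 12 | 9 | 9.0, 84% | 12.1, 83% |

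The listed model's rejection rates also contain the standard-error problem of Step 3. To separate the two, give the averaged effect its correct standard error: 20 × √((1 + 0.5)/2) × √(2/50) = 3.46. Then 6 / 3.46 = 1.73, and the rejection rate is about Φ(1.73 − 1.96) = 41%. So with a correct covariance, the second row would still be called significant about 41% of the time despite no week-12 difference.

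**Step 3: type I error if rows are treated as independent.** Let ρ be the residual correlation between the two visits. The protocol does not give it, so a range is assumed. The true variance of a patient's two-visit mean is σ²(1 + ρ)/2, while the independent-rows model uses σ²/2. Hence the actual two-sided error is 2 × [1 − Φ(1.96 / √(1 + ρ))].

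| ρ (assumed) | Formula | Simulation, 41 per group | Simulation, 50 per group |
|---|---|---|---|
| 0.2 | 7.4% | 8.0% | 7.4% |
| 0.3 | 8.6% | 8.7% | 8.7% |
| 0.5 | 11.0% | 11.0% | 10.8% |
| 0.7 | 13.3% | 14.4% | 14.4% |
| 0.8 | 14.4% | 15.0% | 14.1% |

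(4,000 runs per cell.) The error reaches 10% when 1 + ρ = (1.96 / 1.645)² = 1.42, that is at ρ of about 0.42. ANCOVA on week 12 alone stayed between 4.6% and 5.5% throughout.

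**The case against.** The best defence is that the article is a condensed account. It refers to a pre-established analysis plan that is not shown, the model sentence itself opens by placing the primary analysis at week 12, and a list of factors does not exclude interactions. The authors may intend a repeated-measures model from which the week-12 contrast is taken.

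Part of this stands. Silence about a patient term or covariance is normal in an article, so a reader who infers that the plan has a type I error of about double the nominal level goes too far. That figure needs independent rows, which the text does not state, and a correlation near 0.42, which it does not give. A patient-level covariance would remove the inflation.

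The defence does not remove the first point. The text names the factors down to gender and site and puts week 6 into the primary model. It gives no term or contrast that would return the analysis to week 12. A within-patient covariance alone repairs the standard errors but leaves the coefficient an average.

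A reader might also infer that the continuous secondary outcomes estimate the wrong quantity in the same way. The protocol does not support that. No time levels are listed for those models and no single week-12 target is declared for them. Their schedules also differ: DASH, pain and range of motion at 6 weeks, 12 weeks and 12 months, strength without week 6, and ultrasound measurements at 12 months only.

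**Conclusion.** The point holds for the primary model as written. Its group effect is the mean of the week-6 and week-12 differences and conflicts with the week-12 target set elsewhere in the article. This rests only on the listed terms and does not depend on any correlation. The size of the error is half the gap between the two visits' differences: 6 points, or half the 12-point planning difference, when one visit shows 12 and the other 0, and nothing when the two are equal. The protocol does not indicate which case to expect.

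The type I error of about 7% to 14% is conditional on independent rows and an assumed ρ of 0.2 to 0.8. It is a risk to be closed by wording, not an established property of the plan.

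Because the sentence governs the confirmatory test, it should be corrected before the analysis.

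**What to change.** Choose one of the following and state it in the analysis plan.

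- Fit the primary ANCOVA to week-12 change only. Drop time, and keep group, baseline WORC, site, age and gender. This matches the single-visit sample size calculation.
- Or use a repeated-measures model with group-by-time and a within-patient covariance, and declare the week-12 group contrast the sole primary estimate. An unstructured covariance and a baseline-by-time term are reasonable options, but the inconsistency can be resolved without them.

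In either case, report week 6 as secondary. For continuous secondary outcomes measured at several visits, name the visits, estimate the group contrast at each one, and account for within-patient correlation.

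The cost is about one paragraph of wording, dated before the blinded analysis. No further data, patients or visits are needed.

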Thus, the US investigation at 12 months involves quantitative measures of the repaired and contralateral SST thickness and neovascularity (NV), in addition to the SAS measured as the acromiohumeral distance (AHD). Ultrasound images are captured with the patients seated in an upright position, feet flat on the floor, neutral trunk posture, and head facing forward. For the SST thickness measure the patient has the hand on the affected side on the ipsilateral posterior hip with the humerus in extension and the tendon is measured in a longitudinal [72] and a transverse view [67]. AHD is measured in the neutral position (arm resting at the side) and respectively with 45° and 60° of active shoulder elevation in the scapular plane [72, 73]. SST neovascularity assessed by power Doppler is measured with the shoulder internally rotated with the dorsal side of the hand placed on the sacrum, and the elbow flexed and directed laterally [74].

Registered demographic data include age, gender, tendon(s) involved, supplementary surgery performed, hand dominance, history of trauma, occupation/employment and preoperative sports/recreational activity level. Demographic data and baseline measures will be used in the analysis of predictors of health outcomes.The investigator or site personnel monitor each patient for adverse events (AEs) throughout the study. Tendon re-tear is assessed by US at 6 weeks postoperatively and any re-tear is recorded. The investigator assesses and records any AE (in response to a query, observed by site personnel or reported spontaneously by the patient) in detail, including the date of onset, description, severity, duration and outcome, relationship of the AE to study intervention and any action(s) taken. All AEs will be followed closely to make sure that the patient is safely handled including follow up on clinical issues, until a stable situation is reached.

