### Interim analysis and early stopping rules

An early stopping rule will be applied when there is complete rotator cuff re-tears corresponding to at least 25% of the calculated number in the PR group as verified by ultrasonography 6 weeks postoperatively, provided that the re-tear rate is more than twice as high compared to that in the control UC group [79]. The trial steering committee (the authors of this manuscript) decide if the early stopping rule should be effectuated.

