### Safety monitoring

No data monitoring committee has been established since adverse events are expected to be minimal and the intervention is not considered to be high risk. The physiotherapists at each center will report any adverse event to the primary investigator, who reports these to the ethics committee. The person responsible for randomization will monitor if the number of adverse events has reached the threshold for the early stopping rule. Further, if a patient experiences extreme worsening of symptoms during exercise therapy and these symptoms have not subsided before the next exercise session, the physiotherapist will report it to the primary investigator, who may refer the patient to an orthopedic specialist for an evaluation. The number and seriousness of AEs will be reported.

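### Ordinary logistic regression is the only named between-arm analysis of complications and re-tear, yet few events are expected and it has no finite odds ratio when an arm has none

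*Protocol article*

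**What the plan says.** The Statistical analysis plan section of the Protocol article assigns one method to the binary secondary outcomes: "Secondary outcome measures will be analyzed by multiple logistic regression for binary outcome measures (re-tear, tendon healing, recurrence of symptoms (e.g. pain and function), complications". The same sentence then turns to ANCOVA for the continuous outcomes and ends "with group allocation and time as fixed factors, and site and baseline values as covariates". It is not clear whether that clause also governs the logistic models. The section does not say whether Wald, score or likelihood-ratio tests will be used.

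On how many events to expect, Safety monitoring says "No data monitoring committee has been established since adverse events are expected to be minimal". It gives no rate, and promises "The number and seriousness of AEs will be reported".

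For re-tear, the Outcome measures/variables section says "Tendon re-tear is assessed by US at 6 weeks postoperatively and any re-tear is recorded". No expected re-tear rate is given. The only re-tear figure is the alarm level under Interim analysis and early stopping rules: "complete rotator cuff re-tears corresponding to at least 25% of the calculated number in the PR group", provided that the rate is also more than double that in usual care (UC).

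Arm size comes from Sample size and power considerations: "With an expected dropout around 20% during the study we will randomize and allocate 100 patients (50 to each group".

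**The concern.** The article expects few events, has small arms, and fixes a method that breaks down when events are few. With no events in one arm, the likelihood keeps rising as the group coefficient goes to infinity. There is then no finite odds ratio and no usable Wald interval. If both arms have no events, the model cannot be fitted at all.

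The safety question is whether early active loading leads to more complications or re-tears. Events under progressive rehabilitation (PR) and none under UC would be the clearest sign of that, and it is where the named model gives no estimate. The p value then depends on which test the software prints.

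**Working it through.** **Inputs.** From the article: 50 per arm, 1:1 allocation, about 20% dropout (50 × 0.8 = 40 per arm), two-sided 5% level. Assumed, because the article gives none: event rates of 2% to 25% per arm.

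**The plan's own figure.** The article states no figure for complications or re-tear. As a check on the arm size, its 85% power for the primary outcome reproduces: SE = 20 × √(2/50) = 4, 12/4 = 3, Φ(3 − 1.96) = 0.85.

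**Step 1: how often an arm has no events.** P(no events in one arm) = (1 − p)^n. P(at least one such arm) = 1 − [1 − (1 − p)^n]².

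| Assumed rate, both arms | (1 − p)^50 | At least one empty arm, n = 50 | Same, n = 40 |
|---|---|---|---|
| 2% | 0.364 | 60% | 69% |
| 5% | 0.077 | 15% | 24% |
| 10% | 0.005 | 1% | 3% |

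The 60% includes 13% of trials in which both arms have no events. Exactly one arm is empty in 46% of trials at 2% and in 14% at 5%.

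**Step 2: one worked data set, 6/50 v 0/50, unadjusted.**
- Wald: the fit stops at a log odds ratio of 22.6 with SE about 18,500, so p is about 1 (0.999).
- Likelihood ratio: 2 × [6 ln 0.12 + 44 ln 0.88 − (6 ln 0.06 + 94 ln 0.94)] = 2 × (−18.35 + 22.70) = 8.70, p = 0.003.
- Fisher's exact test: p = 0.027.
- Risk difference: 12 points. The Wilson limits are 5.6% to 23.8% for 6/50 and 0% to 7.1% for 0/50. The Newcombe lower limit is 12 − √[(12 − 5.6)² + 7.1²] = 2.4 and the upper limit is 12 + (23.8 − 12) = 23.8.
- Firth: in a two-group model this adds 0.5 to each cell. OR = (6.5 × 50.5)/(0.5 × 44.5) = 14.8, log OR 2.69, finite.

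At 3/50 v 0/50 the tests also disagree: Wald 0.999, likelihood ratio 0.039, Fisher 0.24.

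**Step 3: rejection rates.** These come from exact enumeration with 50 per arm and unadjusted tests: the sum, over all pairs of counts, of the product of the two binomial probabilities for the pairs that reject at 0.05. An empty arm counts as a Wald non-rejection. Firth uses the penalised likelihood-ratio test, and Newcombe rejects when its interval excludes zero.

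| Rates | Wald | Likelihood ratio | Firth | Newcombe | Fisher |
|---|---|---|---|---|---|
| 5% v 5% (size) | 0.2% | 8.8% | 4.3% | 2.1% | 0.7% |
| 10% v 10% (size) | 2.4% | 6.1% | 4.8% | 3.7% | 1.8% |
| 12% v 2% (power) | 12% | 61% | 51% | 44% | 31% |
| 25% v 10% (power) | 48% | 53% | 51% | 50% | 41% |

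At a 5% rate the Wald test almost never rejects and the ordinary likelihood-ratio test rejects too often. Firth is closest to nominal size. Fisher is more conservative than Wald at 10% v 10% and has less power at 25% v 10%.

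**The case against.** The strongest reply is that this is a condensed article. It refers to a separate analysis plan fixed in advance, where the test and any sparse-data fallback would normally be set. Logistic regression for binary secondary outcomes is also not wrong in itself. The absence of a fallback is indeed no error. What remains is that the article names a method and, in Safety monitoring, expects the situation in which that method fails.

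Four stronger readings are tempting, and the document does not support them.

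- **That a clear excess would be reported with p near 1.** This is true of the Wald test only, and the article does not name Wald. The likelihood-ratio test from the same model gives 0.003 at 6 v 0.
- **That regression is the only way harm would be seen.** It is the only named between-group model, but the number and seriousness of adverse events will be reported and any re-tear recorded, so 6 v 0 would show in the counts. Counts alone give no interval for the difference.
- **That re-tears will be sparse.** The expectation of few events concerns adverse events in general. The 25% figure for re-tear is an alarm level and not a forecast, but nothing supports a rate as low as 2%. At 25% v 12.5%, exactly one arm is empty in 0.1% of trials. At 13/50 v 3/50, Wald and Fisher both give 0.012.
- **That many covariates make it worse.** The covariate clause may belong to the ANCOVA only. An empty arm causes the failure with or without covariates.

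Replacing the model with Fisher's exact test as lead analysis is not the answer either, as Step 3 shows.

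**Conclusion.** The point holds in limited form. The named analysis fails in a situation that the article itself expects: few events and at most 50 patients per arm. How often depends on a rate that the article does not give: 60%, 15% and 1% of trials have at least one empty arm at assumed rates of 2%, 5% and 10%. Short of an empty arm, low rates still leave the conclusion dependent on an unnamed test, with sizes of 0.2% (Wald) and 8.8% (likelihood ratio) at a 5% rate.

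The concern is strongest for complications. It is weak for re-tear if its rate is 10% or more. The sizes and powers assume unadjusted tests and 50 per arm. This is a secondary and safety analysis matter, and the primary outcome is unaffected.

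**What to change.** For complications and re-tear, state that the report gives counts by arm and the between-arm risk difference with a Newcombe (score) 95% CI. Fit any odds ratio by Firth-penalised logistic regression with profile-likelihood intervals and tests, with terms limited to group and the stratification factors (site and age group). Do not make Fisher's exact test the lead analysis. Add that a non-significant result is read from the confidence limits and is not evidence of equal safety.

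The cost is a sentence or two in the analysis plan, with no new data and no change to any clinical rule. The downside is that the risk difference is unadjusted and the penalised odds ratio is slightly shrunk. If the unseen analysis plan already contains such a provision, it is enough to align the article's wording with it.
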